###### **3.13. Trial Procedures and Evaluations**

###### **3.13.1. Pre-Study Screening**

Potential participants will access a screening survey through REDCap which will be a preliminary measure of their eligibility for the study. Once a participant has completed the REDCap screening form, participants who appear eligible will be contacted via phone for a pre-screening call to give them additional background information on the study and associated participant responsibilities. The study coordinator will also complete the Clinician-Administered PTSD Scale for DSM-5 (CAPS-5) and Posttraumatic Stress Disorder Checklist-4 (PCL-4) over the phone. Participants will be sent the informed consent form (ICF) via email after the call. If participants agree to participate in the study, they will email the signed ICF to the study team. Participants who meet all major inclusion/exclusion criteria will be invited to the Interventional Psychiatry Program at St. Michael’s Hospital for an in-person screening. Eligibility will be assessed during the screening and eligibility confirmation visits, which will be scheduled during the pre-screening call. Any questions will be answered at this point. The timeline of visits will then be explained. Additionally, the use of the wearable device will be explained. The participant will be asked if they have any additional questions. Once all questions have been answered, the participant will be asked if they are still interested in participating in the study. The in-person screening visit will then be scheduled.

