###### **3.2.2. Eligibility Criteria**

###### **3.2.3. Inclusion Criteria: Individuals eligible to be enrolled into this protocol are participants who:**

1. Meet Diagnostic and Statistical Manual-5th edition (DSM-5) criteria for current PTSD with a duration of 6 months or longer assessed by study psychiatrist;
2. Have a Clinician-Administered PTSD Scale for DSM-5 (CAPS-5) score of 50 or higher, indicating moderate to severe PTSD symptoms;
3. Between the ages 18 and 65, inclusive;
4. Are willing to refrain from taking any psychiatric medications during the study period, with the exception of gabapentin when prescribed for pain control. If the subject is on stimulants for attention-deficit/hyperactivity disorder (ADHD) at baseline, they can continue to use them at the same dose and frequency as long as they discontinue 5 half lives before the psilocybin session and do not restart for 10 days after psilocybin administration. Any psychoactive drugs, including stimulants, will be tapered in an appropriate fashion to avoid withdrawal effects. Medications will only be discontinued after consultation with the study psychiatrist;
5. Agree that, for one week preceding the psilocybin session, they will refrain from:
   1. taking any herbal supplement (except with prior approval of the research team);
   2. taking any nonprescription medications (with the exception of non-steroidal anti-inflammatory drugs or acetaminophen) unless given prior approval from the research team);
   3. taking any prescription medications (with the exception of birth control pills, thyroid hormones or other medications approved by the research team);
6. Refrain from the use of any psychoactive drug, with the exception of caffeine or nicotine, within 24 hours of the psilocybin session;
7. Agree not to use caffeine or nicotine for 2 hours before and 6 hours after the dose of psilocybin;
8. Agree not to use alcohol for 14 hours before and 24 hours after the dose of psilocybin;
9. Agree not to use benzodiazepines, hypnotics, and mood stabilizers for 12 hours before and 12 hours after the dose of psilocybin;
10. Agree not to use steroids for 2 weeks before and 2 weeks after the dose of psilocybin;
11. Agree not to use s-Adenosyl methionine (SAM-e), 5-Hydroxytryptophan (5-HTP), St. John’s Wort for 1 week before and 1 week after the dose of psilocybin;
12. Agree not to use cannabis for 1 week before and 1 week after the dose of psilocybin;

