###### **3.3. Participant Screening**

Participants will be screened at the Interventional Psychiatry Program at St. Michael’s Hospital, Unity Health Toronto. Before screening, participants will sign a print version of the ICF. Then, participants will undergo screening to confirm eligibility. Participants who are not eligible during the screening will be allowed to re-try on a case by case basis.

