###### **3.13.2. Screening**

Participants will be screened initially to evaluate eligibility for the study at the Interventional Psychiatry Program at St. Michael’s Hospital. All participants will be seen approximately four weeks prior to the first therapy session. The screening visit will last around 2-3 hours. Before any study procedures are undertaken, participants will be given time to ask any questions, and written consent will be obtained by the study coordinator. The participant will also be sized for the wearable device to confirm that the appropriate size is available. However, they will not be given the ring at this visit - should they meet eligibility criteria after review, they will be given the appropriate sized wearable device at their next visit (see section 3.13.3 Eligibility Confirmation).

During the screening visit, all participants that have consented to receiving psilocybin-assisted CPT will:

1. Undergo a physical examination and the measurement of vitals. The examination will involve the following procedures:

- Blood pressure
- Pulse
- Height
- Weight
- Body temperature
- Examination of head, eyes, ears, nose, throat, skin, heart, lungs, abdomen, and extremities
- Brief neurological exam (cranial nerves 2-12, sensory, motor, reflexes and cerebellar function)
- Electrocardiogram (ECG) and 1-minute rhythm strip

1. Provide demographic information and review of medical, psychiatric, and medication history, including review and confirmation of diagnosis.
2. Complete pre-study screening blood work including:

- Hematology: hemoglobin, haematocrit, red blood cell count, white blood cell count (with differential), and platelet count.
- Biochemistry: albumin, alkaline phosphatase, alanine aminotransferase (ALT), amylase, aspartate aminotransferase (AST), bilirubin (total), calcium, cholesterol (HDL, LDL), creatinine, glucose, glycated hemoglobin (HbA1c), potassium, protein (total), triglycerides, sodium, urea (blood urea nitrogen), and uric acid. hCG pregnancy screen (if applicable).
- Immunoassay: insulin.
- Immunology: C-reactive protein.

1. Complete urine to test for certain substances such as non-prescribed drugs. Drug screen results will be kept confidential and will only be disclosed if required by law.
2. Complete the Clinician-Administered PTSD Scale for DSM-5 (CAPS-5). In order for patients to be eligible for the study, their total score should be ≥ 50 (moderate-to-severe PTSD).

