###### **6.4. Informed Consent**

Participants will receive all information required by Health Canada/ICH guidelines, and must be informed that they may withdraw from the study at any time. Individuals must provide written, signed, and dated informed consent to participate in the study. Participants will not be coerced to complete study procedures. The study coordinator will provide them with information about the purpose of the study. The participants will be given sufficient time to read the informed consent form and ask any questions before deciding to participate. Participants who consent to participate in the study will then be asked to sign an informed consent form (ICF). Participants will sign the informed consent as the first step of the screening visit, before doing any study related activities. Additionally, at this visit, participants will be given the credentials of a dummy email account (an email address and password) created by the study team, which they will use to login to the Oura App (if applicable).

The specific consent process is as follows:

1. Informed consent must be obtained prior to any study-specific procedure being conducted on the patient.
2. Obtaining personal written informed consent:
   1. The information is to be given to the subject in written format, the ICF
3. Verify that the ICF given to the potential subject is the most recent REB-approved version of the consent for that clinical trial.
4. The ICF can be first presented to the patient by the study coordinator or other qualified personnel.
   1. The potential subject must be given ample time to read and understand the ICF.
   2. Study staff will then return and discuss the ICF with the potential patient, making sure to highlight important areas of the consent such as:
      1. The purpose of the study.
      2. Explain how many subjects will be involved.
      3. Discuss the duration of the study.
      4. Explain how many visits the subject will make.
      5. Discuss procedures; study intervention, device.
      6. Risks and possible benefits.
      7. Responsibilities of the investigator and subject.
      8. Any compensation to the subject.
      9. Notification of any other treatment available for the condition.
      10. That the subject has the right to withdraw.
      11. Confidentiality.

4. Promote the exchange of information with the subject and encourage any questions.

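### Section 3.13.1 has CAPS-5 and a PTSD checklist completed by phone before the consent form is sent, against the consent-first rule in sections 3.13.2 and 6.4

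*Protocol*

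**What the plan says.** Protocol section 3.13.1 starts with a REDCap survey, followed by a pre-screening call to those who appear eligible. It then states: "The study coordinator will also complete the Clinician-Administered PTSD Scale for DSM-5 (CAPS-5) and Posttraumatic Stress Disorder Checklist-4 (PCL-4) over the phone". The consent form follows: "Participants will be sent the informed consent form (ICF) via email after the call". Its return is by email: "If participants agree to participate in the study, they will email the signed ICF to the study team". The in-person screening visit comes after that.

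Three other sections deal with consent:

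- Section 3.3: "Before screening, participants will sign a print version of the ICF".
- Section 3.13.2, on the screening visit: "Before any study procedures are undertaken, participants will be given time to ask any questions, and written consent will be obtained by the study coordinator".
- Section 6.4, as a general rule: "Informed consent must be obtained prior to any study-specific procedure being conducted on the patient". On timing: "Participants will sign the informed consent as the first step of the screening visit, before doing any study related activities". The numbered steps that follow have staff discuss the form with the person and an investigator join for further questions. The participant and the staff member presenting the form then sign it.

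On the instrument itself, section 3.2.3 lists as an inclusion criterion: "Have a Clinician-Administered PTSD Scale for DSM-5 (CAPS-5) score of 50 or higher, indicating moderate to severe PTSD symptoms".

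**The concern.** Section 3.13.1 puts a clinician-administered trauma interview ahead of the consent form, while sections 3.13.2 and 6.4 put consent ahead of any study procedure. A coordinator who follows the first breaks the other two.

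Participant protection is at stake. Section 3.10.2 describes CAPS-5 as covering the index trauma, the most distressing event and the exposure history, which is more than a short eligibility question. In Table 2 the consent form and the first suicidality assessment (C-SSRS, lifetime and past month) both belong to the screening visit, so a phone CAPS-5 would come before both. An emailed signature would also bypass the discussion with staff and the investigator that section 6.4 describes.

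**Working it through.** No arithmetic bears on the contradiction. The check sets the order of steps in each section side by side.

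| Place | When consent is signed | How | CAPS-5 relative to consent |
|---|---|---|---|
| 3.13.1 | After the pre-screening call, before the visit | Signed form returned by email | Before |
| 3.3 | Before screening | Print version | Not stated |
| 3.13.2 | At the screening visit, before study procedures | Written, obtained by the coordinator | After |
| 6.4 | First step of the screening visit | Signed with staff, after an investigator has joined | After, if CAPS-5 is study-specific or study-related |
| Table 2 | Screening column | Not stated | Same column; no pre-screening column exists |

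**Is the phone CAPS-5 on the call that precedes the form?** Section 3.13.1 does not say so in as many words. It describes only one call, mentions the phone assessments next, and sends the form after the call. No other reading fits the text naturally.

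**Is the phone CAPS-5 a study-specific procedure?** The protocol does not define the term, but four points indicate that it is.

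1. CAPS-5 is the severity criterion in 3.2.3, a secondary outcome in 3.10.2 and the variable of the main efficacy test in 7.1.
2. Study staff give it to people being considered for this trial.
3. Section 3.13.2 lists CAPS-5 among the procedures for people who have already consented.
4. The timing sentence in 6.4 uses wider wording that covers study-related activities of any kind.

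**Is there another consent step that would cover the call?** The protocol describes no verbal consent, waiver or separate pre-screening consent, and it does not call the phone CAPS-5 routine care. Section 3.4 describes the coordinator's contact before the visit as background and time commitment only, with no assessments. The sections therefore also differ on what happens before the visit.

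**Which conflicts of route are firm?** Section 3.3 can be squared with 3.13.1, because a form could be printed, signed and emailed before screening. Section 6.4 cannot: a form already returned signed is not first signed at the visit. Section 3.13.2, which has the coordinator obtain written consent at the visit, conflicts with 3.13.1 in the same way.

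**Two side checks.** Table 2 schedules CAPS-5 twice before treatment, at screening and baseline. With the phone interview it would be given 2 + 1 = 3 times, and the first is unscheduled. The label PCL-4 stands only in 3.13.1. The instrument is PCL-5 in 3.10.2, 3.13.2 and Table 2, so this looks like a typing slip.

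**The case against.** The best defence is that 3.13.1 is headed as pre-study screening and that such steps are not study-specific. It carries little weight: the same instrument, given by the same study team, is treated in 3.13.2 as something done after consent, and the wording of 6.4 reaches study-related activities generally.

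The defence is right to limit the consequences. A reader might infer any of the following, and the protocol does not support them:

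- **That the recruitment rate is inflated.** Sections 3.10.1 and 7.1 define it as participants per month, with a threshold of 2-3. It has no screened denominator, so people excluded by phone cannot change it.
- **That data collected before consent would be unusable.** No section states such a rule, and no planned analysis names the phone scores. CAPS-5 and PCL-5 are collected again at screening and at baseline, and change is measured from baseline.
- **That the phone interview adds selection on the CAPS-5 cut-off.** No phone cut-off is given. Section 3.13.1 assigns the eligibility assessment to the screening and eligibility confirmation visits, and 3.13.2 ties the score of 50 to the screening-visit CAPS-5. Inviting people who meet the major criteria may draw on the phone score, but the text does not say so.
- **That all 15 participants would certainly enter with a consent deviation.** This depends on 3.13.1 being followed as written and on how an undefined term is read.

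**Conclusion.** The contradiction stands. Section 3.13.1 places CAPS-5 and the checklist before the consent form is sent, sections 3.13.2 and 6.4 require consent first, and nothing in the protocol bridges the gap. The consent route is also inconsistent between 3.13.1 on one side and 3.13.2 and 6.4 on the other.

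The conclusion rests on two readings: that the phone assessments belong to the single call described, and that CAPS-5 given by study staff to candidates for the trial is a study procedure. On those readings, everyone assessed by phone is affected, whether later enrolled or not.

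No effect on an endpoint or on the recruitment rate is shown. The one reporting consequence is modest. Section 3.2.5 defines a screen failure as someone who signed the consent form and was then found ineligible. Anyone excluded on the phone before signing falls outside that category, so the screening flow is described incompletely. The point should be corrected before enrolment because it concerns consent, and the correction is simple.

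**What to change.** Choose one of two routes in section 3.13.1:

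1. Remove CAPS-5 and the checklist from the pre-screening call. Section 3.13.2 already has CAPS-5 and PCL-5 at in-person screening, so no scheduled measurement is lost.
2. Keep them, but after documented consent. This may be a consent step for the call approved by the research ethics board. If the full form is to be signed before the visit, the statement in 6.4 that it is signed as the first step of the visit has to change, and the investigator and staff steps there have to be fitted to a remote signature.

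Under either route, state one timing and one method of consent in 3.3, 3.13.1, 3.13.2, 6.4 and Table 2, and make section 3.4 agree on what the contact before the visit contains. Correct PCL-4 to PCL-5. If a phone interview stays, add it to Table 2 and report how many people were assessed and excluded at that step.

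The cost is a reordered step and consistent wording. Dropping the phone interview would mean a few more in-person screen failures; the protocol gives no figure from which to estimate how many.

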###### **3.13.2. Screening**

Participants will be screened initially to evaluate eligibility for the study at the Interventional Psychiatry Program at St. Michael’s Hospital. All participants will be seen approximately four weeks prior to the first therapy session. The screening visit will last around 2-3 hours. Before any study procedures are undertaken, participants will be given time to ask any questions, and written consent will be obtained by the study coordinator. The participant will also be sized for the wearable device to confirm that the appropriate size is available. However, they will not be given the ring at this visit - should they meet eligibility criteria after review, they will be given the appropriate sized wearable device at their next visit (see section 3.13.3 Eligibility Confirmation).

During the screening visit, all participants that have consented to receiving psilocybin-assisted CPT will:

1. Undergo a physical examination and the measurement of vitals. The examination will involve the following procedures:

- Blood pressure
- Pulse
- Height
- Weight
- Body temperature
- Examination of head, eyes, ears, nose, throat, skin, heart, lungs, abdomen, and extremities
- Brief neurological exam (cranial nerves 2-12, sensory, motor, reflexes and cerebellar function)
- Electrocardiogram (ECG) and 1-minute rhythm strip

1. Provide demographic information and review of medical, psychiatric, and medication history, including review and confirmation of diagnosis.
2. Complete pre-study screening blood work including:

- Hematology: hemoglobin, haematocrit, red blood cell count, white blood cell count (with differential), and platelet count.
- Biochemistry: albumin, alkaline phosphatase, alanine aminotransferase (ALT), amylase, aspartate aminotransferase (AST), bilirubin (total), calcium, cholesterol (HDL, LDL), creatinine, glucose, glycated hemoglobin (HbA1c), potassium, protein (total), triglycerides, sodium, urea (blood urea nitrogen), and uric acid. hCG pregnancy screen (if applicable).
- Immunoassay: insulin.
- Immunology: C-reactive protein.

1. Complete urine to test for certain substances such as non-prescribed drugs. Drug screen results will be kept confidential and will only be disclosed if required by law.
2. Complete the Clinician-Administered PTSD Scale for DSM-5 (CAPS-5). In order for patients to be eligible for the study, their total score should be ≥ 50 (moderate-to-severe PTSD).
3. Complete Columbia Suicide Severity Rating Scale (C-SSRS) lifetime and past month.
4. Complete the Mini International Neuropsychiatric Interview (MINI).
5. Complete Posttraumatic Stress Disorder Checklist-5 (PCL-5).
6. Contraceptive method review.

The routine blood and urine tests will be done to ensure that there are no medical reasons that may make participants ineligible for the study. The purpose of this laboratory test is not for further research, but rather for safety and risk monitoring. If a participant tests positive for pregnancy, they will not be enrolled in the study. Any positive urinary drug test findings that cannot be attributed to pre-approved concomitant medications or diet will be reviewed by the study physician to assess compliance with ongoing eligibility criteria. A full list of screening assessments can be found in Table 2.

###### **3.13.3. Eligibility confirmation**

Eligible participants will be seen in person approximately a week after the screening visit (approximately 3 weeks before baseline) to confirm eligibility and receive the wearable device and access to the wearable app and web-based platform. During or prior to this visit, the study doctor will review laboratory test results and confirm that eligibility criteria are met. Once eligibility is confirmed, the study coordinator will assist the participant with the setup of the wearable app and web-based platform. Participants will be given study email credentials (dummy email address and password), which they will use to log-in to the Oura App. Email forwarding from the dummy email to the participants preferred email account will be set up. The study coordinator will provide an explanation of how to use the Oura app and the web-based platform and answer any questions the participant might have. Participants will wear the ring for approximately 3 weeks after this visit before beginning treatment, which will be referred to as the baseline period. This baseline period is necessary to ensure accurate data collection by the Oura Ring and to establish baseline parameters. Moreover, during this visit, the following items will be collected:

- Concomitant medications
- Columbia Suicide Severity Rating Scale (C-SSRS) since last visit
- Contraceptive method review
- Exclusion/inclusion criteria review

###### **3.13.4. Pre-baseline wearable monitoring (Oura)**

Participants will complete the following scales weekly (week 1-3) between eligibility confirmation and baseline visits for digital monitoring:

- Concomitant medications
- Columbia Suicide Severity Rating Scale (C-SSRS) since last visit
- Posttraumatic Stress Disorder Checklist for the DSM-5 (PCL-5)
- Patient Health Questionnaire-9 (PHQ-9)
- Generalized Anxiety Disorder Scale, 7-item (GAD-7)
- World Health Organization Well-Being Index, 5-item (WHO-5)

###### **3.13.5. Baseline**

Participants will complete baseline assessments one day before day 1. During this visit, baseline scores for the following items will be collected:

- Concomitant medications
- Contraceptive method review
- Columbia Suicide Severity Rating Scale (C-SSRS) since last visit
- Clinician-Administered PTSD Scale for DSM-5 (CAPS-5)
- Posttraumatic Stress Disorder Checklist for the DSM-5 (PCL-5)
- Patient Health Questionnaire-9 (PHQ-9)
- Generalized Anxiety Disorder Scale, 7-item (GAD-7)
- Dissociative Experiences Scale II (DES-II)
- Pittsburgh Sleep Quality Index (PSQI)
- Quality of Relationships Inventory (QRI)
- World Health Organization Well-Being Index, 5-item (WHO-5)
- Psychosocial Functioning (IPF)
- Posttraumatic Maladaptive Beliefs Scale (PMBS)
- Brief Experiential Avoidance Questionnaire (BEAQ)
- 24 items Multidimensional Psychological Flexibility Inventory (MPFI-24)
- Difficulties in Emotion Regulation Scale-Short Form (DERS-SF)
- Self-Compassion Scale-Short Form (SCS-SF)
- Childhood Trauma Questionnaire-short form (CTQ-SF)

